#### Secondary outcomes

##### Mental health outcomes

Secondary outcomes include the mean change in general mental well-being measured with the WHO-5 questionnaire [19], the mean change in symptoms of anxiety measured by the seven-item General Anxiety Disorder questionnaire (GAD-7) [28], and, for patients with diabetes, the mean change in diabetes distress measured by the five-item Problem Areas In Diabetes Questionnaire (PAID-5) [29]. Outcome assessments will be made at baseline and after 6 and 12 months.

##### Somatic outcomes

Somatic outcomes include the mean change in total cholesterol levels (mmol/L), low-density lipoprotein (LDL) levels (mmol/L), and, for patients with diabetes, HbA1c (mmol/mol) from baseline to 12 months.

##### Process outcomes

Process outcomes include measures of implementation: fidelity, dose, reach, and mechanisms of impact: mediators and unintended consequences.

#### Participant timeline {13}

The participant timeline is outlined in Table 1.

#### Sample size {14}

The sample size was calculated according to the following assumptions: We expect 20% of patients with T2D and/or CHD who attend annual chronic care consultations to decline participation or be excluded from the study. We expect 15% of participating patients to report reduced mental well-being (WHO-5 score < 50 points), and 20% of patients participating in the study are expected to be lost to follow-up after 12 months. The intraclass correlation coefficient (ICC) is conservatively estimated at 0.05, reflecting a realistic expectation that a mental outcome is likely to show a larger dependence on the individual general practice than somatic outcomes, where an ICC of 0.01 is often applied. To achieve a significance level of 5% and a power of 90%, the study is required to include a total of 188 patients.

In Denmark, the size of a general practice depends on its number of practice capacities. Each general practice capacity accommodates approximately 1600 patients, with an average of 2.5 practice capacities per practice. Based on these assumptions, we need to include at least 35 practice capacities (corresponding to 14 average-size general practices) to be able to include 188 patients over a 1-year study period.

#### Recruitment {15}

##### Recruitment of general practices

An e-mail describing the study is sent by the national health authorities to all general practices in the Central Denmark Region, and interested general practices can sign up for participation. Additionally, general practices who have previously expressed an interest in participating in mental health studies and/or research projects are contacted directly by the research team.

##### Recruitment of patients

Enrolment of patients relies on the general practices to systematically recruit patients at the annual chronic care consultations. The research team will take a number of initiatives to support the workflow of patient recruitment in each general practice. Prior to commencing the study, initial online meetings will be held between two members of the research team and one GP (practice owner) from each general practice to map the staff composition, current chronic care management, and workflow. Together with the GP, the research team tailors a plan for the management of patient recruitment in each individual general practice. Immediately before the study commencement, a visit is paid to each general practice to inform healthcare professionals and administrative staff about the study and facilitate the implementation of the tailored recruitment plan. One healthcare professional from each general practice is appointed the study contact person and study champion, responsible for patient recruitment and implementation of the intervention. Subsequently, videos demonstrating how to provide oral and written information to patients will be distributed to general practices. Throughout the study period, monthly newsletters are forwarded to the participating general practices with general information about the study and individual statistics regarding patient enrolment and number of conducted PST sessions during the intervention period. Patient recruitment is monitored weekly by the research team and champions are promptly contacted by e-mail, telephone, or a visit in case recruitment rates decline, to explore the underlying reasons and support further recruitment.

### Assignment of interventions: allocation

#### Sequence generation {16a}

A computer-generated cluster randomisation is applied at the general practice level. Randomisation includes stratification by number of practice capacities and geographical location.

#### Concealment mechanism {16b}

Due to the nature of the intervention design, concealment is not possible.

#### Implementation {16c}

The allocation sequence is generated by a statistician independent of the research team. Details regarding participant and patient enrolment are outlined in the “Recruitment {15}” section.

### Assignment of interventions: blinding

#### Who will be blinded {17a}

Due to the nature and design of the intervention, blinding is not applicable. To avoid a potential impact on the healthcare providers’ professional behaviour, they only receive cursory information about PST during the control period.

#### Procedure for unblinding if needed {17b}

Blinding is not applicable in this study.

### Data collection and management

#### Plans for assessment and collection of outcomes {18a}

Information about patients is entered into the Healthy Mind website database by healthcare professionals upon enrolment. For patients with a WHO-5 score > 50 points, sex, age, and diagnosis (T2D and/or CHD) are registered. For patients with a WHO-5 score < 50 points, additional registration of social security number, name, contact information, and WHO-5 score is made.

##### Mental health outcomes

Upon enrolment, an automatically generated link to a questionnaire is sent out to participating patients with a WHO-5 score < 50 points. The questionnaire assesses the primary and secondary mental health outcomes as described above. This link is sent via email/SMS at baseline, as well as after 6 and 12 months. Reminders are sent to non-responders by email/SMS after 1 and 2 weeks, followed by a reminder telephone call after 3 weeks. Patients who are unable to access the electronic questionnaire are provided with an identical paper version at baseline and receive follow-up paper questionnaires by mail after 6 and 12 months. The questionnaires are forwarded to the research team and entered manually into the Healthy Mind database by a data manager independent of the research team. Non-responders to mailed questionnaires receive a reminder telephone call after 3 weeks. The Healthy Mind database mandates that all questionnaire items must be completed before submission, and duplicate registrations cannot be entered, ensuring comprehensive and accurate registrations. More detail on questionnaire properties is provided in Table 2.

**Table 2 Tab2:** Overview of mental health outcomes in questionnaires at baseline and after 6 and 12 months

Questionnaire	Number of items	Range	Cut-off values	Measure
**PHQ-9**^a^	9	0–27	0–5: no depression 5–10: mild depression 10–15: moderate depression 15–20: moderately severe depression > 20: severe depression	Depressive symptoms
**GAD-7**^a^	7	0–21	0–4: minimal anxiety 5–9: mild anxiety 10–14: moderate anxiety > 15: severe anxiety	Anxiety symptoms
**PAID-5**^b^	5	0–20	> 7: elevated diabetes distress	Diabetes distress
**WHO-5**^c^	5	0–100	< 50: impaired mental well-being	Mental well-being

^a^4-point Likert scale (0 = not at all; 3 = nearly all of the time)

^b^5-point Likert scale (0 = not a problem; 4 = serious problem)

^c^6-point Likert scale from (0 = none of the time; 5 = all of the time)

##### Somatic outcomes

Somatic outcomes are obtained through the local LABKA II database, which contains all results of blood samples analysed in the Central Denmark Region.

##### Process outcomes

The process outcome data are part of an explanatory sequential mixed methods process evaluation, guided by the UK Medical Research Council framework for process evaluations [30, 31]. Quantitative process outcome data are collected continuously throughout the study via the Healthy Mind website database. Information about fidelity and dose is collected through questionnaires completed by healthcare providers during the registration following each PST session. Reach data are extracted from trial-monitoring records, while data on mediators and unintended consequences come from questionnaires completed by both healthcare providers and patients after the patient’s final PST session.

Qualitative data will be collected through semi-structured interviews with purposefully selected patients (*n* = 10) after their final PST session. The interview guide will focus on reach, fidelity, mediators, and unintended consequences and will be informed by quantitative process measures from each individual patient. Qualitative interview data will be transcribed verbatim and analysed thematically. The process evaluation will be supplemented by ethnographic case studies exploring the role of context.

##### Co-variates

At baseline, the Brief Health Literacy Scale for Adults (B-HLA) [32] is applied to measure the level of health literacy. Socioeconomic status data is obtained from the national registers.

#### Plans to promote participant retention and complete follow-up {18b}

General practices receive remuneration for providing information (written and oral), screening eligible patients and completing PST sessions. Remuneration will match the standard remuneration for equivalent services. This incentive will facilitate continuous patient recruitment and delivery of the intervention.

Moreover, healthcare providers are encouraged to monitor patient attendance and ensure that new PST sessions are scheduled upon cancellation or non-attendance.

The number of questionnaire items is kept at a minimum to prevent item attrition, and both electronic and paper questionnaires are available.

#### Data management {19}

In compliance with the General Data Protection Regulations (GDPR), the study is listed in the record of processing activities at Aarhus University (journal number: 2016–051-000001) [33]. Upon completion of data collection, the data set will be checked for errors, which will be resolved if possible. Computers and servers used for data management will be password-protected. The secure data management system and the Healthy Mind website database are provided by Aarhus University. Data from registers are managed through IT infrastructure provided by Statistics Denmark in accordance with the data management agreement between Statistics Denmark and Aarhus University.

#### Confidentiality {27}

Data collection, storage, and access will comply with the GDPR regulations [33]. Access to the collected data will only be granted to members of the research group.

#### Plans for collection, laboratory evaluation, and storage of biological specimens for genetic or molecular analysis in this trial/future use {33}

No collection of biological specimens for genetic or molecular analysis is made in this study.

## Statistical methods

### Statistical methods for primary and secondary outcomes {20a}

#### Primary outcome

The comparative analysis will estimate the mean change in PHQ-9 score from baseline to follow-up at 6 and 12 months. A linear mixed model will be used, adjusting for patients’ age, gender, and socioeconomic status. The cluster effect by general practice and the correlation between repeated measurements on the same patient over time will be taken into account in the multilevel analysis [34].

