#### Secondary outcomes

##### Mental health outcomes

The mean change in WHO-5, GAD-7, and PAID-5 (for patients with diabetes) scores from baseline to follow-up at 6 and 12 months will be estimated using the same methods as for the primary outcome.

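### The stated PHQ-9 model adjusts for neither baseline PHQ-9 nor the randomisation strata; unless it holds baseline means equal between conditions, it gives up precision that is free to recover

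*Protocol article*

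**What the plan says.** The primary outcome is change in PHQ-9 to 6 and 12 months, and the statistical methods section of the Protocol article analyses it in that form: "The comparative analysis will estimate the mean change in PHQ-9 score from baseline to follow-up at 6 and 12 months". The model follows: "A linear mixed model will be used, adjusting for patients’ age, gender, and socioeconomic status". On correlation it says: "The cluster effect by general practice and the correlation between repeated measurements on the same patient over time will be taken into account".

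For WHO-5, GAD-7 and PAID-5, mean change "will be estimated using the same methods as for the primary outcome". The paragraph on cholesterol, LDL and HbA1c refers back to the same demographic, clustering and time terms.

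On allocation, section 16a says: "Randomisation includes stratification by number of practice capacities and geographical location". Neither factor appears in any stated model.

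Baseline PHQ-9 is collected. Of the questionnaire link, section 18a says: "This link is sent via email/SMS at baseline, as well as after 6 and 12 months". The participant timeline (Table 1) also shows baseline values for every secondary scale and laboratory measure.

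**The concern.** The score of the same scale at entry is usually the strongest available predictor of the score at follow-up. The article names three demographic covariates and leaves this one out. Subtracting baseline is not the same as adjusting for it. Subtraction fixes the baseline coefficient at 1, whereas adjustment estimates it, and with a correlation below 1 and similar SDs the best coefficient is below 1.

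Two things are at stake:

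- **Precision.** The treatment contrast has a larger variance than it needs to have, in a trial of 188 patients and about 14 practices.
- **Chance imbalance.** If the groups differ at baseline by chance, part of that difference passes into the change-score contrast through regression to the mean.

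The strata raise a separate and smaller issue: the analysis should reflect the way the practices were randomised.

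**Working it through.** **Inputs from the article.** N = 188, 5% significance, 90% power, ICC 0.05, 20% loss at 12 months, 14 practices, two groups of practices crossing over at 4 and 8 months.

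**Inputs not in the article.** Effect size, SD and the baseline to follow-up correlation r. I take r = 0.3, 0.5 and 0.7 as assumptions.

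**1. The plan's own figure.** The sample size section says: "To achieve a significance level of 5% and a power of 90%, the study is required to include a total of 188 patients" and "The intraclass correlation coefficient (ICC) is conservatively estimated at 0.05". Without an effect size or SD, 188 cannot be reproduced. It can only be solved backwards, here as a simple two-group comparison that ignores the stepped wedge:

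- Patients per practice: 188/14 = 13.4. Design effect: 1 + (13.43 − 1) × 0.05 = 1.62.
- With 20% loss: 188 × 0.8 = 150.4, and 150.4/1.62 = 92.8 effective patients. The standardised difference is (1.960 + 1.282) × √(4/92.8) = 0.67.
- With no loss: 188/1.62 = 115.9, giving 0.60.
- With neither loss nor design effect: 0.47.

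None of these shows whether the calculation assumed change scores or a baseline-adjusted analysis.

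**2. Change score against baseline adjustment, equal SDs.** Per patient, with SD set to 1:

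- variance of a change score = 2(1 − r)
- variance after baseline adjustment = 1 − r²
- ratio = (1 − r²)/[2(1 − r)] = (1 + r)/2

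| r (assumed) | Change score | Adjusted | Ratio | 188 × (1 − ratio) |
|---|---|---|---|---|
| 0.3 | 1.40 | 0.91 | 0.65 | 66 patients |
| 0.5 | 1.00 | 0.75 | 0.75 | 47 patients |
| 0.7 | 0.60 | 0.51 | 0.85 | 28 patients |

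The last column expresses the loss as patients' worth of information at the patient level, before clustering.

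**3. Unequal SDs.** If the follow-up SD is k times the baseline SD, the change-score variance is 1 + k² − 2rk and the adjusted variance is k²(1 − r²). They differ by (1 − rk)², so the loss shrinks as rk approaches 1. With k = 1.2 (assumption) and r = 0.5:

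- change score: 1 + 1.44 − 1.20 = 1.24
- adjusted: 1.44 × 0.75 = 1.08
- ratio: 1.08/1.24 = 0.87, a gain of 13% rather than 25%

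A k above 1 is plausible, because entry is restricted to WHO-5 below 50, which may narrow the spread of PHQ-9 at baseline.

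**4. Baseline as a repeated response.** I computed the generalised least squares variance of the 12-month contrast with three time points, equal correlation r, complete data and 94 patients per condition. Multiplied by 94, it is:

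| r | Baseline means free | Baseline means held equal |
|---|---|---|
| 0.3 | 2.80 | 1.82 |
| 0.5 | 2.00 | 1.50 |
| 0.7 | 1.20 | 1.02 |

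The free version equals 4(1 − r), the change-score result. The constrained version equals 2(1 − r²), the baseline-adjusted result.

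**5. Chance imbalance.** With equal SDs, a chance baseline difference D shifts the change-score contrast by −(1 − r)D: 0.7D, 0.5D and 0.3D in size for r = 0.3, 0.5 and 0.7. Baseline adjustment removes this part.

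**6. Strata.** Same method for the wedge: 14 practices, two sequences, three equal periods, 188/42 = 4.48 patients per practice and period, ICC 0.05, a practice random effect, and four strata (assumption). With period terms:

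- no strata terms: variance 0.07035
- strata fitted but explaining nothing: 0.07112 (+1%)
- strata explaining half the between-practice variance: 0.06728 (−4%)
- strata explaining all of it: 0.06162 (−12%)

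Without period terms, the range runs from about 0% to −4%.

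**7. Power.** Using Φ(3.242/√ratio − 1.960): if 188 gives 90% with change scores, adjustment raises it to 98.0%, 96.3% and 94.0% for r = 0.3, 0.5 and 0.7. Using Φ(3.242 × √ratio − 1.960): if the 90% assumed baseline adjustment, change scores give 74.3%, 80.2% and 84.8%. The article does not say which case applies.

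**The case against.** **The model is not fully stated.** The text describes a longitudinal mixed model with within-patient correlation, and this fits baseline as one of the repeated responses. If baseline means are held equal between conditions, step 4 shows that nothing is lost. This stands. A reader might infer that baseline is certainly only subtracted and that the loss is a fact of the plan. The article does not say so; it leaves open which model is meant.

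**This is analysis-plan detail.** An article may leave model terms to a fuller document. That carries less weight here, because the article gives a specific covariate list and says that it describes the trial in full. As written, the list omits baseline and the strata, and no other section adds them.

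**The strata buy little precision.** This stands. They are constant within a practice, practice is already in the model, and practices contribute both control and intervention patients. A reader might infer a material loss from omitting them. At the stated ICC the figures in step 6 do not show one.

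**The size depends on assumptions.** This also stands: r is assumed, and equal SDs are not assured.

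**Baseline adjustment does not rescue unconcealed recruitment.** Correct. Practice staff enrol patients knowing their own condition, and the baseline questionnaire is completed after enrolment. Where patients recruited under the two conditions differ systematically, neither change scores nor baseline adjustment is sure to be unbiased.

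**Conclusion.** The point holds, with conditions. The stated model has neither baseline PHQ-9 nor the stratification factors as covariates, and it is carried to the other three scales. If it analyses change scores, or lets baseline means differ by condition, its patient-level variance exceeds that of a baseline-adjusted analysis. Adjustment would then cut the variance by 15 to 35% for r from 0.7 to 0.3 with equal SDs, and by about 13% at r = 0.5 if the follow-up SD is 1.2 times the baseline SD. If baseline means are held equal, there is no loss.

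A reader might go further and conclude that the trial is underpowered at 188. The documents do not support that: step 7 points in opposite directions depending on what the calculation assumed, and the article does not tell us.

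The strata belong in the model because the analysis should match the randomisation. Their effect on variance is about 0 to 4% in plausible cases and 12% at the limit. Overall this is a worthwhile improvement to a stated model, not a flaw that invalidates it.

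**What to change.** In the statistical methods for the primary outcome, specify that the 6- and 12-month PHQ-9 scores are the responses, with baseline PHQ-9 as a covariate whose coefficient may differ by visit. Add practice capacities and geographical location as fixed effects alongside age, gender and socioeconomic status. The treatment effect at each visit still reads as a difference in mean change, so the outcome definition need not move. If a repeated-measures model with a common baseline mean was intended, saying so settles the baseline part.

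Use the same form for WHO-5, GAD-7 and PAID-5, each with its own baseline score. For total cholesterol, LDL and HbA1c, use the baseline laboratory value.

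The cost is wording. The baseline measures are already scheduled and the strata are known from randomisation. The strata use a few practice-level degrees of freedom out of about 14 practices, so they should be coded sparingly.

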### Trial design {8}

The study is conducted from November 1, 2022, to January 16, 2024, with follow-up after 6 and 12 months. The design is a stepped-wedge cluster-randomised controlled trial with 1-year follow-up (Fig. 1). General practices are randomised into two clusters. Initially, all participating general practices act as the control group. After 4 months, healthcare professionals in cluster 1 undergo a 2-day PST course, following which they transition to the intervention group and begin offering the intervention to eligible patients. Healthcare providers from cluster 2 attend the PST course after 8 months and will subsequently be part of the intervention group.

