##### Somatic outcomes

Comparative analyses will estimate the mean change in total cholesterol levels (mmol/L), LDL levels (mmol/L) and (for patients with diabetes) HbA1c levels (mmol/mol) from baseline to 12 months using a generalised linear mixed model. The model will consider patient demographics, clustering, and time effects as described above.

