## Discussion

This study will evaluate the impact of providing PST in general practice to patients with T2D and/or CHD and concurrent poor mental well-being. The chosen stepped-wedge cluster-randomised controlled trial design offers practicality and enhances data collection. Firstly, all general practices are guaranteed inclusion in the intervention arm, easing the recruitment process. Secondly, comparison between the two groups will be affected to a minimum by contextual factors, since the general practices and the healthcare professionals are identical. Thirdly, healthcare providers’ motivation to participate in the study during the control period may increase, knowing they will later transition to the intervention phase. Fourthly, cluster-level randomisation helps prevent contamination arising from treatment spillover.

Further, the embedded mixed methods process evaluation offers an in-depth understanding of how the intervention works and for whom. This comprehensive approach provides crucial insights for future implementation and valuable learning points.

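### The stated primary model names no calendar-period effect, so calendar-time differences in PHQ-9 change can bias the PST effect, notably at 6 months

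*Protocol article*

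**What the plan says.** Trial design {8}: "The design is a stepped-wedge cluster-randomised controlled trial with 1-year follow-up". "General practices are randomised into two clusters", and "Initially, all participating general practices act as the control group". "After 4 months, healthcare professionals in cluster 1 undergo a 2-day PST course" and then cross over; "Healthcare providers from cluster 2 attend the PST course after 8 months" and follow. The calendar dates given run from 1 November 2022 to 16 January 2024, about 14.5 months. Sample size {14} speaks of a 1-year study period.

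Statistical methods {20a}, Primary outcome: the mean change in PHQ-9 to 6 and 12 months is estimated with a linear mixed model. The terms named are "age, gender, and socioeconomic status. The cluster effect by general practice and the correlation between repeated measurements on the same patient over time". The other mental health outcomes use the same methods.

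Statistical methods {20a}, Somatic outcomes: "The model will consider patient demographics, clustering, and time effects as described above".

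Discussion, among the advantages of the design: "comparison between the two groups will be affected to a minimum by contextual factors, since the general practices and the healthcare professionals are identical".

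**The concern.** In a stepped wedge the condition is tied to calendar time: control patients are enrolled early and intervention patients late. What is randomised is the crossover date. Only a comparison that allows for period rests on that randomisation. Without a period term, the estimate is largely a before-after contrast within practices.

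The listed terms do not cover this. Practice clustering removes differences between practices. The time mentioned in the primary model belongs to the correlation of repeated measurements within a patient, so it is follow-up time. The somatic section refers back to time effects, but nothing above it defines a calendar effect. The Discussion's argument from identical practices and professionals deals with practice differences and leaves calendar differences untouched.

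The 6-month change is one of the two primary time points (Outcomes {12}) and has its own planned publication (Dissemination plans {31a}).

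**Working it through.** **Plan's own figure.** The 188 patients (5% significance, 90% power, ICC 0.05, 20% loss) cannot be reproduced from the article, which gives no effect size or SD. The check below therefore works in SD units.

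**Inputs from the protocol.** 14 practices; two sequences crossing over at months 4 and 8; ICC 0.05; 188 × 0.8 = 150.4 patients analysed.

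**Assumptions.** 7 practices per sequence, equal practice sizes, even recruitment, constant within-practice correlation, one follow-up measure per patient, two-sided 5% test. The third period lasts 4 months (12-month window) or 6.5 months (14.5-month window).

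**1. Overlap.** Sequence-months recruiting while both conditions are open: 4 + 4 = 8. This is 8/24 = 33% of the 12-month window or 8/29 = 28% of the 14.5-month window.

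**2. How much calendar change enters the estimate.** Generalised least squares on practice-period means, with a random practice effect and no period terms, gives these weights of the treatment estimate on a shift in each period's mean change score:

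| Window | Period 1 | Period 2 | Period 3 | SE (SD units) |
|---|---|---|---|---|
| 12 months | -0.69 | 0 | +0.69 | 0.162 |
| 14.5 months | -0.69 | -0.10 | +0.79 | 0.164 |

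So roughly 70-80% of a shift between the first and last periods is read as treatment effect. With period fixed effects all these weights are 0.

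**3. What cancels.** The weights sum to zero, so anything that adds the same amount to every patient's change drops out.
- Linear trend in PHQ-9 level, a + bt: the 6-month change gains 6b for everyone. Bias 0.
- Annual cycle at 12 months: f(t + 12) - f(t) = 0. Bias 0.

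**4. What does not cancel: season at 6 months.** Take f(t) = 0.5 cos(2π(t - 2.5)/12), with t in months from 1 November. This is a 1-point peak-to-trough swing peaking in mid-January (assumed). The mean of f(t + 6) - f(t) is -0.80 in period 1, +0.21 in period 2, and +0.58 (4-month) or +0.08 (6.5-month) in period 3.
- 12 months: 0.69 × 0.80 + 0 + 0.69 × 0.58 ≈ 0.96 points.
- 14.5 months: 0.69 × 0.80 - 0.10 × 0.21 + 0.79 × 0.08 ≈ 0.59 points.
- Simple arm averages give 0.92 and 0.57.

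The sign is positive: the intervention arm looks worse.

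**5. Type I error, SD 5 (assumed).** Shift of the test statistic δ = bias/(5 × SE); error = Φ(-1.96 - δ) + 1 - Φ(1.96 - δ).
- 12 months: δ = 0.96/(5 × 0.162) = 1.18, error 22% (about 20-21% from the arm averages).
- 14.5 months: δ = 0.59/(5 × 0.164) = 0.72, error 11%.

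**6. Drift in the change score.** If the change itself drifts linearly by 0.3 SD over the window (case mix, recruitment, usual care; size assumed), the bias is 0.14 SD and the type I error about 14% in either window.

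**7. Cost of period terms.** The SE rises to 0.294 (12 months) or 0.319 (14.5 months).
- Variance ratio: (0.294/0.162)² ≈ 3.3; (0.319/0.164)² ≈ 3.8.
- Power for an effect that had 90% without period terms: Φ(3.24 × 0.162/0.294 - 1.96) ≈ 43%; Φ(3.24 × 0.164/0.319 - 1.96) ≈ 38%.
- Standardised difference detectable with 90% power: from 0.53 to 0.95-1.03.

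**The case against.** The model paragraph is condensed. It does not name a treatment indicator or a visit term either, and both are needed, so silence on period need not mean exclusion. The somatic section shows that the authors have some time effect in mind, and a separate analysis plan may define it. This stands to the extent that the list should not be called complete or the omission deliberate. It does not remove the point: the article states an adjustment set and a correlation structure, calendar period is in neither, and the back-reference leads to nothing calendar-based. If an analysis plan adds the term, the published description still needs correcting.

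A reader might infer that every secular or seasonal change in depression is counted as a PST effect. The documents do not support that. The outcome is within-patient change, so the two cancellations in the working apply, and months 4-8 give a concurrent randomised comparison. A reader might also infer a spurious benefit. Under the seasonal pattern assumed here the bias runs against PST; other patterns could go either way.

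The seasonal sizes rest on an assumed swing, SD and recruitment pattern. The upper values use a 12-month window, whereas the stated dates give 14.5 months and the lower ones. The period weights do not depend on the swing or the SD.

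The Discussion sentence gives its own reason, identical practices and professionals, and makes no explicit claim about calendar time. It needs a qualification; deletion would go too far.

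**Conclusion.** The point holds in limited form. Followed as written, the primary analysis and the secondary analyses that borrow from it name no period effect in a design where condition and calendar time are confounded, and the estimate is largely before-after. The exposure is mainly seasonal change at 6 months, plus drift in case mix, recruitment or usual care that alters the change score. The 12-month result is protected from an annual cycle but not from such drift.

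The best-supported seasonal figure, on the stated dates, is a 6-month bias of about 0.6 points with type I error near 11%; a 12-month window gives 0.9-1.0 points and 20-22%. These are illustrations under the stated assumptions. The missing period term in a stated stepped-wedge model is the finding, and it should be corrected before the comparative analysis.

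**What to change.** - **Primary outcome:** add fixed effects for enrolment period (at least the three step periods), by visit, because season acts differently on the 6- and 12-month changes. Carry this to the secondary mental health and somatic models.
- **Somatic outcomes:** define the time effects, separating calendar period from follow-up time.
- **Discussion:** add that identical practices and professionals do not remove calendar-time differences, which the period terms address.
- **Sample size {14}:** restate the power on the model with period effects.

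No new data are needed beyond each patient's enrolment date. The cost is precision, as the last step of the working shows, and it should be declared openly. Settling the term before outcomes are compared also prevents a choice between two models with very different standard errors. Further refinements, such as a practice-by-period random effect or a particular degrees-of-freedom method, are not needed to cure this defect and can be left to the analysis plan; with 188/(14 × 3) ≈ 4.5 patients per practice-period, such a variance component would be poorly estimated.
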